## 11. CALCULATION OF SAMPLE SIZE (This section has been amended. Please refer to the information in “Amendment” section.)

The estimated measurement variability in BMD, muscle (lean mass of left thigh) and functional mobility is 0.72, 0.89 and 0.89, respectively. The minimum expected difference in BMD between BSYJF and placebo is defined to be 0.5. Therefore, a minimum sample size of 37 for BMD, and 55 for lean mass of left thigh and functional mobility, respectively. Each group will provide 90% statistical power at the significance level of 5% in the one-sided test.

For falls, we hypothesize that BSYJF group will lead to an annual 50% reduction, and the incidence of falls among community-dwelling elderly women is considered to 19% in the placebo group according to the previous study (Aoyagi and Ross et al., 1998; Kannus, 1999). A sample size of 110 (55 per

group) is based on a one-sided significance level of 5%, and a power of 90%. Assuming the drop-out rate is 20%, 70 patients per group will be recruited for the trial.

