**All the analyses will use randomly assigned patients under ITT principle. For**

patients missing data after the baseline, the LOCF approach use to analyze the longitudinal data.

The numbers of falls and adverse events will perform by chi-square test. Kaplan–Meier analysis will be calculated in order to demonstrate differences in number of fallers over time. The time to first fall will be analyzed using a Cox regression analysis providing a 95% confidence interval.

Repeated-measures ANOVA analysis should be carried out between two groups and four times (baseline, 12, 24 and 36 months). Within-subjects results will be used *t*-test on the percentage change from the baseline value. All tests will be used two-sided and set at the 5% level.

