| Protocol name        | The effects and safety of Bushen Yijing Fang (BSYJF) reduces hip fractures risk factors in late postmenopausal women with osteopenia: A long-term follow-up, randomized, double-blind and placebo-controlled trial                                                                                                                                                                                                                                                                                                                                                                                                                                                                                                                                                                                                                                                                                                                                                                                                                                                                                                                                                                                                               |
| Sponsor                     | Shanghai Shuguang Hospital                                                                                                                                                                                                                                                                                                                                                                                                                                                                                                                                                                                                                                                                                                                                                                                                                                                                                                                                                                                                                                                                                                                                                                                                              |

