| Design               | Randomized, 36-month, double-blind and placebo-controlled trial with 10 years extension follow-up                                                                                                                                                                                                                                                                                                                                                                                                                                                                                                                                                                                                                                                                                                                                                                                                                                                                                                                                                                                                                                                                                                                                |
| Simple size                 | 140 subjects (70 per group)                                                                                                                                                                                                                                                                                                                                                                                                                                                                                                                                                                                                                                                                                                                                                                                                                                                                                                                                                                                                                                                                                                                                                                                                             |

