| Endpoints                  | 
Endpoints are to be evaluated for BSYJF versus placebo.
 
Primary endpoint:
 
 
1. Number of falls at month 36.
 
 
Secondary endpoints:
 
 
1. Change from month baseline at month 36 in femoral neck BMD;
 
2. Change from month baseline at month 36 in lean mass of left thigh;
 
3. Change from month baseline at month 36 in TUG test;
 
4. Change from month baseline at month 36 in biomarkers of bone turnover (osteocalcin and deoxypyridinoline).
 
5. Change from month baseline at month 36 in endometrial thickness;
 
6. Change from month baseline at month 36 in estradiol;
 
7. Nature, frequency and severity of adverse events and their relationship to treatment.
 
 
Additional endpoint:
 
8. Number of falls at the end of 10 years extension follow-up.
 |
| Statistical considerations | 
All the analyses will use all randomly assigned patients under ITT principle. For patients missing data after the baseline, the LOCF approach use to analyze the longitudinal data. The number of falls at month 36 and adverse events will perform by chi-square test. Kaplan–Meier analysis will be calculated in order to demonstrate differences in number of fallers over time. The time to first fall will be analyzed using a Cox regression
                                                                                                                                                                                                                                                                                                                                                                                                                                                                                                                 |

|  |                                                                                                                                                                                                                                                                                                                                                                                                                                                                                                    |

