|--|----------------------------------------------------------------------------------------------------------------------------------------------------------------------------------------------------------------------------------------------------------------------------------------------------------------------------------------------------------------------------------------------------------------------------------------------------------------------------------------------------|
|  | 
analysis providing a 95% confidence interval. Repeated-measures ANOVA analysis should be carried out between two groups and four times (baseline, 12, 24 and 36 months). Within-subjects results will be used t-test on the mean percentage change from the baseline value. All tests will be used two-sided and set at the 5% level.
 
Additional analysis:
Number of falls at the end of 10 years extension follow-up will be performed by chi-square test.
 |
|--|----------------------------------------------------------------------------------------------------------------------------------------------------------------------------------------------------------------------------------------------------------------------------------------------------------------------------------------------------------------------------------------------------------------------------------------------------------------------------------------------------|

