### Section: 5.1 Study Design

Replace:

The study duration is from January 2000 to December 2004. Subjects will be randomly assigned to receive BSYJF (n=70) or placebo (n=70) with a 1:1 allocation ratio. The study will carry out at the two sites (Institute of Orthopaedics and Traumatology, Shanghai Academy of TCM; and Shuguang Hospital). A total of 140 participants will be selected from two sites to participate in the study.

With:

**The study will be carried out from January 2000 to December 2014, comprised of a 36 month treatment phase and followed by a 10-year extension phase without treatment.** Subjects will be randomly assigned to receive BSYJF (n=70) or placebo (n=70) with a 1:1 allocation ratio. The study will carry out at the two sites (Institute of Orthopaedics and Traumatology, Shanghai Academy of TCM; and Shuguang Hospital). **At the beginning of the study, a total of 140 participants will be selected from two sites to participate in the study.**

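### Adverse events are compared only by a two-sided 5% chi-square test, with no effect estimate or confidence interval, so a non-significant result would not show how much excess harm is ruled out

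*Supplement*

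**What the plan says.** The protocol name in the Amendment 2 synopsis begins "The effects and safety of Bushen Yijing Fang (BSYJF) reduces hip fractures risk factors in late postmenopausal women with osteopenia", so safety is announced alongside effect. The nature, frequency and severity of adverse events, and their relationship to treatment, form a secondary endpoint, and endpoints are to be evaluated for BSYJF against placebo.

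For the comparison, the same synopsis says "The number of falls at month 36 and adverse events will perform by chi-square test", and "All tests will be used two-sided and set at the 5% level". Section 16.3, as replaced by Amendment 1, names the same test. The one interval in the plan belongs to an efficacy analysis: "The time to first fall will be analyzed using a Cox regression analysis providing a 95% confidence interval".

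Women are to be "randomly assigned to receive BSYJF (n=70) or placebo (n=70) with a 1:1 allocation ratio". Section 11, after Amendment 1 deleted the paragraph on bone density, muscle and mobility, rests on falls alone and ends "Assuming the drop-out rate is 20%, 70 patients per group will be recruited for the trial". No expected adverse event rate, safety margin or power for harms is given. Section 13.4 asks whether adverse event rates agree with pre-study assumptions but states none.

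**The concern.** For harms, the useful question is how large an excess the data still allow. A significance test does not answer it. With a sample size chosen for falls, a real excess of an adverse event can easily give p above 0.05, and a bare p-value is then easily reported as no difference between groups. The plan gives the efficacy analysis of time to first fall an interval and gives adverse events none, although harms are where a null result is most readily taken as reassurance. At stake is the comparative safety statement after 36 months of treatment. The primary falls result is not affected.

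**Working it through.** **Inputs from the documents.** Test: chi-square, two-sided 5% (Amendment 2 synopsis; Section 16.3 as amended). Group size: 70 per arm, 1:1 (Section 5.1 as amended). Drop-out: 20% (Section 11), leaving 70 × 0.8 = 56 per arm if drop-outs contribute no adverse event data.

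**Assumed inputs.** Placebo rates of 2% to 25% over 36 months, because the documents give none. The harm examined is a doubling on BSYJF. The unit is a woman with at least one event of the type in question. The plan has no power figure of its own for adverse events to reproduce.

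**Step 1: normal approximation.** With rates p₁ (placebo) and p₂ (BSYJF), mean rate p̄ and n per arm,

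z = [ |p₂ − p₁|·√n − 1.96·√(2p̄(1 − p̄)) ] / √( p₁(1 − p₁) + p₂(1 − p₂) ), power = Φ(z), miss = 1 − Φ(z).

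- 10% v 20%, n = 70: z = (0.10 × 8.367 − 1.96 × 0.505) / 0.500 = −0.306; power 38%, miss 62%.
- 5% v 10%, n = 70: z = (0.05 × 8.367 − 1.96 × 0.3725) / 0.3708 = −0.841; power 20%, miss 80%.

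**Step 2: exact check.** Every pair of binomial counts was enumerated. The uncorrected Pearson chi-square was applied to each, and only rejections in the direction of harm were counted.

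| Placebo v BSYJF (assumed) | Miss, 70 per arm | Miss, 56 per arm |
|---|---|---|
| 2% v 4% | 92% | 94% |
| 5% v 10% | 80% | 84% |
| 10% v 20% | 62% | 68% |
| 15% v 30% | 42% | 51% |
| 20% v 40% | 25% | 35% |
| 25% v 50% | 13% | 21% |

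The approximation and the enumeration agree to within about one point at 70 per arm for placebo rates of 5% and above, and within two points at 2%. With Yates correction, which the plan neither requires nor excludes, the misses at 70 per arm rise to 89% for 5% v 10% and 70% for 10% v 20%.

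**Step 3: size needed.** For 80% power to detect a doubling, the usual two-proportion formula gives 435 per arm at 5% v 10% and 199 per arm at 10% v 20%.

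**Step 4: what an interval would add.** Suppose 7/70 women on placebo and 14/70 on BSYJF have an event.

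- Pearson χ² = 140 × (14 × 63 − 7 × 56)² / (70 × 70 × 21 × 119) = 2.745, so p = 0.098.
- Wilson 95% limits are 12.3% to 30.8% for 14/70 and 4.9% to 19.2% for 7/70.
- The Newcombe interval for the difference of 10 points has lower limit 0.10 − √[(0.200 − 0.123)² + (0.192 − 0.100)²] = −0.020 and upper limit 0.10 + √[(0.308 − 0.200)² + (0.100 − 0.049)²] = 0.219, using unrounded Wilson limits.

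The p-value alone reads as no difference. The interval, −2.0 to +21.9 points, shows that an excess of about 22 points is still compatible with the data.

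Even with equal observed rates, the 95% half-width, 1.96·√(2p(1 − p)/70), is about 7 points at 5%, 10 points at 10% and 13 points at 20%.

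**The case against.** Four arguments can be made for the plan.

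- **The detail may sit elsewhere.** Section 16.2 refers to an analysis plan to be finalised before database lock, and no separate plan is shown. Table layouts and intervals are often left to such a document. This would answer a complaint of missing detail only. Here the protocol itself chooses a method for a listed endpoint, and the choice is a bare significance test.
- **Safety does not rest on this test alone.** A reader might infer from the title that half the trial is about safety and that it is judged only by chi-square. The documents do not support that. The stated purpose is efficacy. Endometrial thickness and estradiol are separate endpoints, vital signs, laboratory values and ECG are assessed (Section 15.2), and the PI reviews site reports every year (Section 13.4). This objection stands, although none of these items bounds the difference in adverse events.
- **The test does not always miss a doubling.** A reader might infer that non-significance is the likely result whenever an event doubles. That is true at assumed placebo rates of 5% to 10% or lower, but not at 15% or more. The rate of any adverse event over 36 months could lie in that higher range.
- **The misreading is hypothetical.** A reader might infer that p above 0.05 is to count as proof of safety. The plan nowhere says so. Frequency is an endpoint, so counts per arm will exist and anyone could derive an interval from them. Low power for harms is also usual in a trial of 140 women, and an interval does not cure it.

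The 56-per-arm column is a pessimistic case, because analyses are to use all randomised women and Section 14 provides annual follow-up for death and hospitalisation, with permission, after discontinuation.

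**Conclusion.** The point holds in a limited form. A two-sided 5% chi-square test is the only inferential method named for adverse events, without an effect estimate or interval. If placebo rates are 5% to 10%, it misses a doubling about 80% to 62% of the time with 70 per group; across assumed rates of 2% to 20% the miss runs from about 92% down to 25%. These figures depend on assumed rates, the uncorrected Pearson test and one count per woman. What follows is that a non-significant p-value alone would leave the excluded excess of harm unstated. It does not follow that the trial has no other safety evidence or that it intends to equate non-significance with safety. This is a minor, cheap improvement.

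**What to change.** In Section 16.3 and the synopsis, replace the adverse event test with estimation. For women with any adverse event, any serious adverse event, any treatment-related event and each common event type, report the number and percentage per arm and the BSYJF minus placebo risk difference with a 95% confidence interval (Newcombe or score; exact for rare events). Keep the chi-square p-value as descriptive only, and add a sentence that a non-significant difference will not be taken as evidence of safety.

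The cost is a few lines of text and some table columns, with no new data, visits or participants. The downside is that the intervals will be wide and the safety statement will read less favourably.

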### 3. BACKGROUND AND RATIONALE

#### 3.1 Hip fractures

Hip fractures cause disability and even mortality in community-dwelling elderly women, which is a devastating consequence of osteoporosis (Cooper and Barker, 1995; Zuckerman, 1996). Although many factors contribute to such fractures, the most important causes are a reduction in bone mass and an increased frequency of falls (Chapuy and Arlot et al., 1992). It is estimated that approximately 90% hip fractures in late postmenopausal women resulted from a fall (Zuckerman, 1996). It has been known that the deteriorated muscle and impaired functional mobility increases the falling risk factors obviously (Greenspan and Myers et al., 1994). Thus, it indicates that the bone-dependent risk factors including decreased bone mass and deteriorated bone micro-architecture are not the only determinant of hip fracture. In other words, the bone-independent risk factors including decreased muscle and functional mobility also play an important role in hip fracture risk factors in late postmenopausal women.

The conventional medications for preventing hip fractures only focus on bone-dependent risk factors by either inhibiting bone resorption (bisphosphonates) or promoting bone formation (rhPTH). Despite that supplement of vitamin D has demonstrated beneficial effects on muscle, there is still lack of high quality evidence to support that vitamin D alone could prevent hip fractures effectively, especially for the late postmenopausal women with osteopenia (Chapuy and Arlot et al., 1992). Therefore, it is desirable to develop alternative medications that can exert beneficial effects on reducing both bone-dependent and bone-independent risk factors.

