### 7.4 Screening and Baseline Assessment

After ICF has been obtained at the first pre-randomization visit, the consented participant will undergo initial screening which will include basic medical and

medication history, and hip BMD measurement.

At the end of the first pre-randomization visit, the consented participant will be scheduled for a second visit within about 1 week for screening. The participant will be asked to do transvaginal ultrasound and blood test to check endometrial thickness, and kidney and liver function, etc. A venous blood sample (approx. 10 ml) will be taken for blood biochemistries and a urine sample to determine if the individual meets eligibility criteria. A screening log will be recorded by each site to each candidate.

The assessment will be included:

- Medical and medication history(including history of falls);
- Physical examination (including height and weight);
- 12-lead ECG;
- Vital signs: blood pressure, temperature, pulse and heart rate;
- DXA scan of proximal femur;
- Samples: blood count, liver and kidney function, 25 (OH) vitamin D, osteocalcin, 17 $\beta$ -estradiol and urine deoxypyridinoline;
- Safety.

At the third visit, those participants who meet the eligibility criteria will be enrolled in the trial and continue with a further baseline assessment and randomization.

All participants who enter into the screening period will receive a unique subject identification number. Participants numbers will be assigned in sequential order. The subject identification number must remain constant throughout the clinical trial, that's to say, it must not be changed at the time of re-screening, enrollment, or randomization. This number will not be the same as the randomization number assigned for the study. All the participants must be subjected to physical examination, efficacy and safety assessment during the recruitment.

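### The primary falls comparison is an unadjusted chi-square although fall history and baseline TUG are recorded before treatment; pre-specified adjustment would give a modest gain at almost no cost

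*Supplement*

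**What the plan says.** Amendment 1 made falls the only primary endpoint. The latest analysis text is the synopsis in Amendment 2, under Statistical considerations: "The number of falls at month 36 and adverse events will perform by chi-square test". Time to first fall gets a Cox model. In section 16.3 as replaced by Amendment 1 the wording is: "The time to first fall will be analyzed using a Cox regression analysis providing a 95% confidence interval". No model terms are listed for it. The same text sets the error rate: "All tests will be used two-sided and set at the 5% level".

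Two relevant variables are recorded before treatment:

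- Section 7.4 lists, among the screening assessments, "Medical and medication history(including history of falls". The updated Table 1 in Amendment 2 also ticks falls at week 0. No analysis is assigned to this information.
- The same Table 1 ticks the TUG test at week 0. In the analysis, baseline TUG serves only the secondary endpoint of change in TUG.

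On mobility, section 3.1 states that "deteriorated muscle and impaired functional mobility increases the falling risk factors obviously", and section 12.2 presents TUG as the measure of functional mobility. Section 8.1 describes randomisation from random number tables and mentions no stratification.

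**The concern.** When a baseline variable predicts the outcome, including it in the model sharpens the treatment comparison and removes the part of the observed difference that comes from unequal groups at entry. Prior falls are the baseline counterpart of the primary endpoint, and the protocol itself points to mobility as a cause of falls. With 70 women per group and no stratification mentioned, nothing in the design keeps the number of prior fallers similar in the two groups, and the named primary test cannot correct for a difference.

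At stake are some power in a comparison that appears short of it, and the robustness of the one primary result to a chance imbalance that readers would see in the baseline table. If covariates are first chosen after such an imbalance is seen, the choice is post hoc. Naming them now avoids that.

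**Working it through.** **1. The plan's own figure.** The falls paragraph of section 11 still stands, because Amendment 1 deleted only the paragraph on BMD, lean mass and mobility. Its inputs are "the incidence of falls among community-dwelling elderly women is considered to 19% in the placebo group" and "we hypothesize that BSYJF group will lead to an annual 50% reduction". It arrives at 55 per group, "based on a one-sided significance level of 5%, and a power of 90"%. Recomputed per group for 90% power with the usual two-proportion formula, without continuity correction:

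| Reading of the inputs | Risks | n, one-sided 5% | n, two-sided 5% | Two-sided power at 55 / 70 |
|---|---|---|---|---|
| One year, as written | 19% v 9.5% | 231 | 283 | 30% / 36% |
| Annual risk compounded over 36 months | 46.9% v 25.9% | 89 | 109 | 63% / 74% |
| Annual risk tripled | 57% v 28.5% | 50 | 62 | 87% / 94% |

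The 55 is not reproduced exactly by any of these. Tripling comes close (50, or 57 with continuity correction), but neither the tripling nor the correction is stated. The dropout step is consistent: 55/0.8 = 68.75, so 69, and 70 are recruited.

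**2. Unadjusted power on the compounded reading (an assumption).** p1 = 1 − 0.81³ = 0.469, p2 = 1 − 0.905³ = 0.259, difference 0.210, mean risk 0.364.

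z = [0.210√n − 1.96√(2 × 0.364 × 0.636)] / √(0.469 × 0.531 + 0.259 × 0.741)

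At n = 55, z = (1.556 − 1.333)/0.664 = 0.335, so power is 63%. At n = 70, z = (1.755 − 1.333)/0.664 = 0.635, so power is 74%.

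**3. Power with adjustment.** The documents give no odds ratio, correlation or prevalence, so these are assumed: 20% of women with prior falls, TUG standardised, and the odds ratios in the table. There were 2,000 simulated trials per row. The comparison is the uncorrected chi-square against a likelihood-ratio test of treatment in a logistic model with both covariates, two-sided 5%, at 46.9% v 25.9%.

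| Odds ratio: prior falls / per SD of TUG | 55 per group | 70 per group |
|---|---|---|
| 1 / 1 | 64.8% → 64.3% | 73.8% → 74.6% |
| 2 / 1.3 | 65.4% → 66.9% | 74.8% → 76.0% |
| 3 / 1.5 | 65.8% → 69.6% | 73.7% → 76.3% |
| 4 / 2 | 63.1% → 70.1% | 73.6% → 79.0% |

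One simulated power has standard error √(0.65 × 0.35/2000) = 1.1 points, and the first row shows that differences of up to about 1 point appear with no prognostic effect at all. The gain is therefore about 0 to 7 points. At the 12-month risks of 19% v 9.5% it is about 1 to 6 points, on a base of about 30% (55 per group) or 37% (70 per group). No setting reaches 90%.

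**4. Chance imbalance.** With 20% prior fallers and 70 per group, the between-group difference in that proportion has SD √(2 × 0.2 × 0.8/70) = 6.8 points. One trial in 20 exceeds 1.96 × 6.8 = 13 points in one direction or the other. With an odds ratio of 3 and an overall placebo risk of 46.9%, the risks are 41.6% without and 68.1% with prior falls. An imbalance of 13.25 points then moves the risk difference by 0.1325 × 26.5 = 3.5 points, which is 17% of the planned 21 points. Over prevalence 10–30% and odds ratios 2–4, the range is 8–24%.

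**The case against.** The strongest case against is that an unadjusted chi-square in a randomised trial is valid and its type I error already allows for chance imbalance. That is right. The point is about efficiency and robustness, and nothing here makes the planned test wrong.

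Four other limits also stand.

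- A reader might infer that the Cox model adjusts for neither variable. The documents do not support that. The text lists no model terms, and section 16.2 refers to a pre-defined analysis plan, not shown, to be finalised before database lock. All that can be said is that no covariates are named. For the primary endpoint the test itself is named, and it admits none.
- A reader might expect a large gain from the general rule that variance falls by the factor 1 − ρ². At ρ = 0.5, power would rise from 63% to 76% (55 per group) or from 74% to 85% (70 per group). No document supports that correlation. The odds ratios assumed above imply ρ of about 0.17–0.19, 0.27–0.28 and 0.37–0.38, so 0.5 is not reached even in the strongest setting.
- Section 6.2 excludes women with impaired gait, balance, transfer skills or muscle strength. This narrows the spread of baseline TUG and probably its predictive value. Prior falls are not an exclusion, but no passage says how well they predict later falls.
- A reader might think protection against imbalance holds whatever the prognostic strength. It does not. If prior falls barely predict later ones, an imbalance in them barely moves the result.

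**Conclusion.** The point holds as a modest, nearly free improvement. The primary analysis as written cannot use two baseline variables that the trial already collects, and no covariates are named for the Cox model. The likely gain is about 0 to 7 points of power under the assumed odds ratios and 20% prevalence of prior falls, with 36-month risks obtained by compounding. There is some protection against an imbalance in prior fallers, to the extent that they are prognostic.

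A reader might infer that adjustment would cure the shortfall from 90% power. It would not. The shortfall comes from the sample-size inputs in section 11 and from planning one-sided while testing two-sided, and it needs its own correction. Its size depends on how the annual risks are carried to 36 months, which section 11 does not say.

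**What to change.** In section 16.3 and the synopsis, before unblinding:

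- Make the 36-month comparison of fallers a logistic regression on treatment, with prior faller (yes/no, from the screening history) and continuous baseline TUG as fixed covariates. If the number of falls is what is analysed, use a count model with the same covariates.
- For the logistic model, report a risk difference standardised over the trial population, so that the target stays marginal and does not become a conditional odds ratio.
- Put the same two covariates in the Cox model for first fall.
- Keep the chi-square as a supporting, unadjusted result.

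The cost is a short addition to the analysis text and two degrees of freedom, with no new data, visits or participants. The one piece of real work is to define the fall-history variable in advance, because section 7.4 gives neither a look-back period nor a coding.
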